# Testing the implementation and sustainment facilitation (ISF) strategy as an effective adjunct to the Addiction Technology Transfer Center (ATTC) strategy: study protocol for a cluster randomized trial

**DOI:** 10.1186/s13722-017-0096-7

**Published:** 2017-11-17

**Keywords:** Implementation strategies, External facilitation, Type 2 hybrid trial

## Abstract

**Background:**

Improving the extent to which evidence-based practices (EBPs)—treatments that have been empirically shown to be efficacious or effective—are integrated within routine practice is a well-documented challenge across numerous areas of health. In 2014, the National Institute on Drug Abuse funded a type 2 effectiveness–implementation hybrid trial titled the substance abuse treatment to HIV Care (SAT2HIV) Project. Aim 1 of the SAT2HIV Project tests the effectiveness of a motivational interviewing-based brief intervention (MIBI) for substance use as an adjunct to usual care within AIDS service organizations (ASOs) as part of its MIBI Experiment. Aim 2 of the SAT2HIV Project tests the effectiveness of implementation and sustainment facilitation (ISF) as an adjunct to the Addiction Technology Transfer Center (ATTC) model for training staff in motivational interviewing as part of its ISF Experiment. The current paper describes the study protocol for the ISF Experiment.

**Methods:**

Using a cluster randomized design, case management and leadership staff from 39 ASOs across the United States were randomized to receive either the ATTC strategy (control condition) or the ATTC + ISF strategy (experimental condition). The ATTC strategy is staff-focused and includes 10 discrete strategies (e.g., provide centralized technical assistance, conduct educational meetings, provide ongoing consultation). The ISF strategy is organization-focused and includes seven discrete strategies (e.g., use an implementation advisor, organize implementation team meetings, conduct cyclical small tests of change). Building upon the exploration–preparation–implementation–sustainment (EPIS) framework, the effectiveness of the ISF strategy is examined via three staff-level measures: (1) time-to-proficiency (i.e., preparation phase outcome), (2) implementation effectiveness (i.e., implementation phase outcome), and (3) level of sustainment (i.e., sustainment phase outcome).

**Discussion:**

Although not without limitations, the ISF experiment has several strengths: a highly rigorous design (randomized, hypothesis-driven), high-need setting (ASOs), large sample size (39 ASOs), large geographic representation (23 states and the District of Columbia), and testing along multiple phases of the EPIS continuum (preparation, implementation, and sustainment). Thus, study findings will significantly improve generalizable knowledge regarding the best preparation, implementation, and sustainment strategies for advancing EBPs along the EPIS continuum. Moreover, increasing ASO’s capacity to address substance use may improve the HIV Care Continuum.

*Trial registration* ClinicalTrials.gov: NCT03120598.

**Electronic supplementary material:**

The online version of this article (10.1186/s13722-017-0096-7) contains supplementary material, which is available to authorized users.

## Background

### Background and rationale for the implementation and sustainment facilitation experiment

Improving the extent to which evidence-based practices (EBPs)—treatments that have been empirically shown to be efficacious or effective—are integrated within routine practice is a well-documented challenge across numerous areas of health [1–5]. A comprehensive systematic review of studies on the costs and efficiency of integrating HIV/AIDS services with other health services noted, “Unfortunately, few of the studies found adequately address the central questions currently concerning many program managers at this moment in time: not whether to integrate, but when to, how to and which model is most efficient in which setting?” [6]. The need to address these central questions about the integration of substance use disorder (SUD) services within HIV care settings is particularly pressing, given the high prevalence of substance use [7–9] and associated problems among individuals living with HIV/AIDS [10–17].

In 2013, the National Institute on Drug Abuse (NIDA) sought to fund research that would advance understanding of how best to improve the integration of SUD treatment services within HIV/AIDS service delivery settings [18]. In 2014, NIDA funded a type 2 effectiveness–implementation hybrid trial called the substance abuse treatment to HIV Care (SAT2HIV) Project [19]. As shown in Fig. 1, Aim 1 of the SAT2HIV Project tests the effectiveness of a motivational interviewing-based brief intervention (MIBI) for substance use as an adjunct to usual care within AIDS service organizations (ASOs) as part of its multisite MIBI Experiment [20]. Aim 2 of the SAT2HIV Project tests the effectiveness of implementation and sustainment facilitation (ISF) as an adjunct to the Addiction Technology Transfer Center’s (ATTC) model for training staff in motivational interviewing as part of its ISF Experiment. The current paper describes the study protocol for the ISF Experiment and has been written in accordance with the SPIRIT guidelines [21, 22] (see Additional file 1). A cluster randomized design with staff randomized within clusters of ASOs was used to minimize the likelihood of contamination across study conditions. Importantly, although randomization was at the cluster level (i.e., organization level), our objective and hypotheses pertain to staff-level outcomes. The study protocol for the MIBI Experiment, also written in accordance with the SPIRIT guidelines, has been published separately [20]. With this background, we describe below the objective, design, and methods for the SAT2HIV Project’s ISF Experiment.

**Fig. 1 Fig1:**
[figure not shown]
Conceptual overview of the ISF experiment within the context of the parent SAT2HIV Project. *Note*: MIBI motivational interviewing-based brief intervention; *ISF* implementation and sustainment facilitation; *UC* usual care; bolded arrows represent hypothesized relationships; dashed arrows represent interactions and cross-level interactions that will be examined

### Rationale for the ISF Experiment’s EBP, outcomes, and strategies

#### Rationale for the targeted EBP

The selection of motivational interviewing as the to-be-implemented EBP was based on several factors, including (a) research reviews supporting the effectiveness of motivational interviewing in reducing substance use [23–25], (b) the availability of psychometrically sound measures for assessing the extent to which motivational interviewing was implemented with adherence and competence [26], and (c) a research review suggesting that HIV care settings have been receptive to implementing motivational interviewing for HIV medication adherence [27].

#### Rationale for the primary outcomes

Proctor et al. [28] defined “implementation outcomes” as the effects of deliberate and purposeful actions to implement new treatments, practices, and services. However, our interest in comparing the effectiveness of the two strategies during the preparation phase, implementation phase, and sustainment phase of the exploration–preparation–implementation–sustainment (EPIS) continuum [29] required selection of unique preparation, implementation, and sustainment outcomes. Building on prior preparation research [30], days-to-proficiency was selected as the ISF experiment’s primary preparation outcome. Klein and Sorra’s implementation effectiveness construct (i.e., the consistency and quality of targeted organizational members’ use of an innovation) [31] was selected as the ISF experiment’s primary implementation outcome. Implementation effectiveness is important, given it has been hypothesized to be a function of implementation strategies and implementation climate [32–34]. Finally, building on sustainment research that has used raw units (e.g., number of staff trained, number of clients served) to operationalize sustainment outcomes [35], the raw unit of MIBIs delivered during the project’s sustainment phase was selected as the ISF experiment’s primary sustainment outcome.

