#### Eligibility criteria

To be eligible to participate, an ASO (i.e., the cluster) had to (1) serve a minimum of 100 individuals living with HIV/AIDS per year, (2) have at least two case management staff who were willing to be trained in the MIBI for substance use (hereafter referred to as BI staff) [20], and (3) have at least one leadership staff (e.g., supervisor, manager, director) willing to help ensure BI staff were given sufficient time for project participation. There were no exclusion criteria.

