### Outcomes

Table 7 describes the three staff-level outcome measures (i.e., time-to-proficiency, implementation effectiveness, and level of sustainment) used to examine the extent to which the ISF strategy serves as an effective adjunct to the ATTC strategy. Additionally, Table 7 describes the two staff-level measures (i.e., personal recovery status and motivational interviewing experience) and four organizational-level measures (i.e., readiness for implementing change, implementation climate, leadership engagement, and tension for change) that have been hypothesized as moderators of the relationship between organizational condition assignment (ATTC vs. ATTC + ISF) and each respective primary outcome measure.

**Table 7 Tab7:** Instruments, instrument-related procedures, and measures

Measurement instrument	Measurement instrument time points and procedures					
	Staff survey #1 (t = month 0)	Preparation phase assessment (t = months 1–6)	Implementation phase assessment (t = months 7–12)	Staff survey #2 (t = month 13)	Staff survey #3 (t = month 19)	Measure name (purpose) Description
Independent Tape Rater Scale [26]		X^a^				Time to proficiency (preparation outcome) A continuous staff measure representing the number of days between completion of the workshop training by BI staff and their demonstration of proficiency [26, 30] in the motivational interviewing-based brief intervention (MIBI)
Independent Tape Rater Scale [26]			X^b^			Implementation effectiveness [31] (implementation outcome) A continuous staff measure representing the sum of the standardized cumulative number of MIBIs delivered by BI staff (i.e., consistency) and the cumulative integrity score of their delivery of the MIBI (i.e., quality)
Staff survey	X^c^			X^c^	X^c^	Level of sustainment (sustainment outcome) A continuous staff measure (no specified range) that represents the number of MIBIs a BI staff self-reports having delivered during the past 6 months
Staff survey	X^c^			X^c^	X^c^	Motivational Interviewing Experience (moderator variable) A staff measure indicating a BI staff’s perception of their motivational interviewing experience (0 = none, 1 = beginner, 2 = intermediate, 3 = advanced, 4 = expert)

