#### Recruitment

The identification and recruitment of ASOs was conducted by the Principal Investigator (BG) and project coordinators (DK, EB). Potential ASOs were identified via searches of organization directories [89, 90]. Identified ASOs were sent standardized introduction emails, with follow-up calls completed as necessary by project coordinators. ASOs interested in learning more about the project participated in a 45- to 60-min, organization-specific, Web-assisted, informational webinar, which was conducted by the Principal Investigator or one of the project coordinators.

In addition to providing information about the project, a key goal of the informational webinar was to gather information about the ASO, including (a) whether describing their organization as a community-based ASO was accurate, (b) the key services provided to individuals living with HIV/AIDS, (c) the number of individuals living with HIV/AIDS served annually, (d) the number of case-management staff, (e) their level of interest in participating in the project, and (f) their reasons for wanting to participate. Upon review of the collected information, the Principal Investigator and project coordinators identified ASOs that did not represent a good fit for the project. ASOs deemed to be a good fit were contacted via email and/or phone, and official participation was documented by having the ASO’s signing official sign and date a project participation agreement.

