### Assignment of interventions

#### Allocation

Participating ASOs were assigned to one of two study conditions via urn randomization [91]. Using staff survey data collected during the exploration phase from the BI staff and leadership staff, seven organizational-level factors (importance of substance use screening, importance of brief intervention for substance use, innovation-value fit, implementation strategy-value fit, implementation climate for substance use brief intervention, implementation readiness for substance use brief intervention, and implementation effectiveness for substance use brief intervention) were entered into the urn randomization program gRAND [92], which optimized the balance of the two study conditions on these seven factors. Written consent was obtained from BI staff and leadership staff before survey completion.

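### Both MIBI volume outcomes lack a measure of opportunity; a pre-randomization caseload covariate already gathered at recruitment would protect power if delivery tracks caseload

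*Protocol article*

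**What the plan says.** Under Rationale for the primary outcomes, the article states that "the raw unit of MIBIs delivered during the project’s sustainment phase was selected as the ISF experiment’s primary sustainment outcome". Table 7 (Outcomes) defines the measure as one that "represents the number of MIBIs a BI staff self-reports having delivered during the past 6 months". The same table defines implementation effectiveness as "the sum of the standardized cumulative number of MIBIs delivered by BI staff (i.e., consistency) and the cumulative integrity score". It does not say what the count is standardized against, and neither measure has a denominator.

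On size, Eligibility criteria requires an ASO to "serve a minimum of 100 individuals living with HIV/AIDS per year" and sets no upper limit. Under Allocation, seven organizational factors built from baseline staff surveys went into an urn program, "which optimized the balance of the two study conditions on these seven factors". Neither ASO size nor caseload is named among them. The last two listed are "implementation readiness for substance use brief intervention, and implementation effectiveness for substance use brief intervention) were entered into the urn randomization program".

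Under Recruitment, the informational webinar gathered, among other items, "the number of individuals living with HIV/AIDS served annually, (d) the number of case-management staff". These figures therefore precede randomization. The Statistical methods section specifies an intention-to-treat analysis in HLM software and names no covariates.

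**The concern.** Staff can deliver MIBIs only to clients they see. If two staff members convert opportunity into delivery at the same rate but one has twice the clients, the raw count differs twofold for a reason unrelated to ISF. With 39 ASOs and two BI staff in each, such differences add to between-ASO variance, which is what limits a cluster trial. Arms may also differ in opportunity by chance.

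At stake is the power of the arm comparison on two of the three primary outcomes, and how easily an observed difference can be read. The stated power calculation uses an ICC of .05, which leaves little room for between-ASO variation in a count.

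**Working it through.** **1. The plan's own figure.** Inputs from Sample size: J = 39 ASOs, m = 2 staff, ICC ρ = .05, p < .05 (taken as two-sided), effect size δ = .67. The noncentrality is λ = Jδ² / {4[ρ + (1 − ρ)/m]} = 39 × 0.4489 / (4 × 0.525) = 17.507 / 2.1 = 8.34, on 1 and 37 df. Power is 80.3% and the detectable effect at 80% is 0.668. The stated .67 reproduces.

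**2. Sensitivity to the ICC.** With δ held at .67 SD:

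| ICC | Power | Detectable effect at 80% |
|---|---|---|
| .05 | 80.3% | 0.668 |
| .10 | 78.4% | 0.683 |
| .20 | 74.9% | 0.714 |
| .30 | 71.5% | 0.743 |

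Under the assumptions in step 4, caseload variation moves the ICC of the raw count from about .05 to .08–.28.

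**3. Chance imbalance in opportunity.** The documents give no caseload spread, so assume a log-caseload SD of 0.5 to 0.8 and simple, near-equal allocation with respect to caseload. The SE of the arm difference in mean log caseload is 2 × SD / √39:
- SD 0.5: 0.160, and exp(1.96 × 0.160) = 1.37.
- SD 0.8: 0.256, and exp(1.96 × 0.256) = 1.65.

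The arms' geometric mean caseloads can thus differ by a factor of up to 1.37 to 1.65 within the 95% chance range.

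**4. Power with and without the covariate.** Simulated trials of 39 ASOs with two staff each. Assumptions: control mean 5 MIBIs, residual ASO log-SD 0.25, staff overdispersion 1, true 2.5-fold effect, caseload known without error. Both analyses are linear models of the raw count, so the scale is the same and only the covariate differs.

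| Dependence of delivery on caseload | Log-caseload SD | Raw count | With log caseload |
|---|---|---|---|
| Proportional | 0.5 | 70–74% | 80–82% |
| Proportional | 0.8 | 50% | 68% |
| Square root | 0.5 | 85–88% | gain within 2–5 points |
| Square root | 0.8 | 78–80% | gain within 2–5 points |
| None | 0.5–0.8 | 90–91% | loss of about 1–2 points |

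Ranges reflect repeated runs at the same settings.

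**5. Type I error.** With no ISF effect, the linear model of the raw count rejects in 4–5% of trials. A separate simulation with a mean of 20 MIBIs and ASO size CV of 0 to 1.0 gave 4.3–5.1%.

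**The case against.** The strongest case against the point has five parts.

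- **Covariates belong to the analysis plan, which is not shown.** This is true of covariate lists in general. Here, however, the article fixes the outcome's unit as a raw count, and the proposal improves on that choice with data already gathered. Volume delivered is a legitimate target, so the outcome itself need not change.
- **A floor on total clients says nothing about clients per case manager.** This stands. Larger ASOs may employ more case managers. A reader might infer from the eligibility rule that caseloads vary several-fold, but the documents do not show it. Nor do they show that an ASO-wide ratio tracks the caseload of the two BI staff.
- **Some balance may exist already.** One urn factor is baseline implementation effectiveness for substance use brief intervention, and the surveys record brief interventions delivered. The factor may carry part of the delivery volume. How it was scored is not stated, so this is possible and not established.
- **Randomization protects the comparison.** This stands. A reader might infer that caseload would mimic an ISF effect or bias the test. Type I error stays near 5%, and the p value and confidence interval already allow for chance imbalance. What remains is lost precision and a result that is harder to read.
- **Larger gains can be shown only by changing two things at once.** In the proportional case at SD 0.8, one set of runs gave 49% for the raw linear count, 65% on the log scale without caseload, and 84% on the log scale with it. Of that 35-point gain, 16 points come from the scale alone. Only the same-scale contrast in step 4 measures the covariate.

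Calling both outcomes raw would also be inexact, since the consistency part is standardized. If that means ordinary z-scoring, it only rescales and leaves relative differences between ASOs intact.

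**Conclusion.** The point holds as one of conditional power and interpretability. Neither volume measure has a denominator, ASO size has no ceiling, and neither size nor caseload is named in the allocation. If delivery depends on caseload, the raw-count comparison loses power that a covariate could partly recover: about 8 to 18 points under proportional dependence and 2 to 5 under square-root dependence, at a log-caseload SD of 0.5 to 0.8. If caseload is irrelevant, adjustment costs about 1 to 2 points.

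These figures rest on an assumed caseload spread, control mean, overdispersion and 2.5-fold effect, and on error-free caseload. An approximate webinar figure would recover less. The documents do not support a claim that caseload will swamp or mimic the ISF effect, or that the randomized test is invalid.

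**What to change.** For level of sustainment and for the count part of implementation effectiveness, pre-specify log(annual clients living with HIV / number of case-management staff) as an ASO-level covariate in the linear model, before any outcome comparison by arm.

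- Estimate its coefficient freely. An offset would force delivery to be proportional to caseload, which nothing in the documents supports.
- Use only the value recorded at the recruitment webinar. Later screening or caseload figures could themselves be changed by ISF.
- Keep the raw count as the sustainment outcome, and report the unadjusted result beside the adjusted one.

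The cost is one degree of freedom (37 to 36 at ASO level) and about 1 to 2 points of power if caseload does not matter. The covariate is an approximate, ASO-wide stand-in for the opportunity of two particular staff members. The article says the figures were gathered but not how they were stored, so their completeness for all 39 ASOs should be confirmed first.

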#### Rationale for the strategies tested

Guidance for strategy selection was drawn from the research of Miller et al. [30], which experimentally compared strategies for training individuals in motivational interviewing. Relative to the other conditions examined (e.g., workshop training, workshop plus feedback, workshop plus coaching), the most effective condition for helping individuals demonstrate proficiency in motivational interviewing was the workshop training plus feedback plus coaching condition. Given its empirical support, each of these discrete strategies is encompassed within the overarching strategy of centralized technical assistance that ATTCs across the United States use in training individuals in motivational interviewing [36] (hereafter referred to as the ATTC strategy).

Although the staff-focused ATTC strategy is viewed as necessary for helping staff learn motivational interviewing, we argue that it may be insufficient on its own for optimizing the preparation, implementation, and sustainment processes. As such, we sought to identify an effective adjunct to the ATTC strategy. Each of the discrete strategies identified by Powell et al. [37] were considered as potential adjuncts to the ATTC strategy. Use of an improvement or implementation advisor was selected as the overarching strategy-to-be-tested, as Gustafson et al. [38] found that of the strategies compared, clinic-level coaching (i.e., use of an improvement advisor) was the best strategy for decreasing patient wait-time and increasing the number of new patients. In addition, six other discrete strategies (develop tools for quality improvement, organize implementation team meetings, identify and prepare champions, assess for readiness and identify barriers, conduct local consensus discussions, and conduct cyclical small tests of change) were packaged with the implementation advisor and branded together as the ISF strategy.

### The ISF Experiment’s Objective and Scientific Hypotheses

Testing the effectiveness of the ISF strategy as an adjunct to the ATTC strategy is the ISF Experiment’s key objective. Table 1 lists the planned scientific hypotheses for the ISF Experiment, which were guided by use of a decomposed-first strategy [39] that advocates for starting with moderation-focused hypotheses to avoid biases associated with conflated effects.

**Table 1 Tab1:** Planned scientific hypotheses

Hypotheses	
H1	The positive relationship between the implementation and sustainment facilitation and staff time-to-proficiency will be moderated by
	H1a Staff’s motivational interviewing experience
	H1b Staff’s personal recovery status
	H1c Organization’s readiness for implementing change
	H1d Organization’s implementation climate
	H1e Organization’s leadership engagement
	H1f Organization’s tension for change
H2	The positive relationship between the implementation and sustainment facilitation and staff implementation effectiveness will be moderated by
	H2a Staff’s motivational interviewing experience
	H2b Staff’s personal recovery status
	H2c Organization’s readiness for implementing change
	H2d Organization’s implementation climate
	H2e Organization’s leadership engagement
	H2f Organization’s tension for change
H3	The positive relationship between the implementation and sustainment facilitation and staff level of sustainment will be moderated by
	H3a Staff’s motivational interviewing experience
	H3b Staff’s personal recovery status
	H3c Organization’s readiness for implementing change
	H3d Organization’s implementation climate
	H3e Organization’s leadership engagement
	H3f Organization’s tension for change
H4	Staff implementation effectiveness will mediate the relationship between staff time-to-proficiency and staff level of sustainment

